### Interventions

After enrollment, eligible patients will be randomly assigned to receive twice daily QFGKG 12.0 g or twice daily dummy QFGKG (placebo) 12.0 g. The use of placebo as a comparator in this trial largely depends on empirical evidence [17, 28, 29] and Guidelines for Clinical Research of New Chinese Medicine [26]. Besides, the absence of generally recognized therapy and self-healing tendency of PIC also support the use of placebo. QFGKG and placebo in this trial are manufactured by Baotou TCM Co., Ltd. The Latin names, English names and Chinese Pinyin of the four herbs used in QFGKG are listed in Table 6. Both within-group changes and between-group changes are assessed across three time-points during treatment. As to the treatment duration, a longer (14 days) treatment in part A is conducted for the sake of more cured cases, while a shorter treatment (10 days) in part B is enough for monitoring noticeable changes in cough symptom score. A two-day follow-up will be conducted for all patients. At the initial drug dispensing stage, patients are advised to strictly follow protocol instructions, which will be reiterated at each study visit. Participants are requested to genuinely report their daily dosage of drugs that have been actually taken and to return unused ones to physicians at each study visit. Drug using and returning will be recorded on CRF by physicians. Unused drugs will be finally collected and counted by drug managers and then be destroyed by the sponsor at the end of the trial. All previous and concomitant treatments, including drug and non-drug therapies, taken one week before and during the intervention will be recorded on CRF. Concomitant treatment for comorbidities such as hypertension, diabetes and other chronic conditions are permitted during the intervention. Whereas, the use of antibiotics, Western or other antitussives, and non-drug cough suppressing therapies such as acupuncture and cupping are strongly discouraged to prevent potential systemic effects. Participating centers are required to record dropout cases and reasons, and also side effects happen during the intervention.

**Table 6 Tab6:** Latin name, English name and Chinese pinyin of the four herbs

Latin name	English name	Chinese pinyin
*Ephedra sinica Stapf*	Herba Ephedrae	Ma Huang
*Sinomenium acutum*	Caulis Sinomenii	Qing Feng Teng
*Stemona japonica (Blume) Miq.*	Radix Stemonae	Bai Bu
*Aster tataricus L.f.*	Aster tataricus	Zi Wan

### Outcome measures

#### Part A

##### Primary outcome

The primary outcome of part A is time to cough resolution, i.e. the time to the first day when cough completely disappears. Cough resolution is defined as both daytime cough symptom score nighttime cough symptom score graded as 0, for 48 h. If the total cough symptom score is classified as 0 in the two successive days, the previous day should be considered as the first day when cough completely disappears (Note: cough symptom score is used to assess cough symptoms within the last 24 h). For example, if the total cough symptom score of a patient is rated as 0 on the fifth day and the sixth day after intervention, then the time to cough resolution is regarded as five days.

##### Secondary outcomes

Secondary outcomes of interest in part A include cough symptom score, time to cough relief and TCM curative effect. Cough relief is defined as both daytime cough symptom score and nighttime cough symptom score ≤ 1 or reduce by one score, for 48 h. TCM curative effect is calculated as percentage of cumulative TCM symptom score reduction (PSSR) estimated between baseline and post-intervention, which is categorized into four grades, complete recovery (PSSR ≥ 95 %), excellent effect (95 % > PSSR ≥ 70 %), modest effect (70 % > PSSR ≥ 30 %) and no effect (PSSR < 30 %). The TCM symptom score system used in the protocol follows the Guidelines for Clinical Research of New Chinese Medicine [26], in which primary and secondary symptoms are given graded scores. The TCM symptom score and TCM signs system is provided in Fig. 2. TCM signs will also be assessed, but not scored. PSSR is calculated according to the following formula:

**Fig. 2 Fig2:**
[figure not shown]
TCM symptom score and TCM signs

$$ \mathrm{PSSR}=\left(\frac{symptom\kern0.5em  score\kern0.5em  before\kern0.5em  treatment- symptom\kern0.5em  score\kern0.5em  after\kern0.5em  treatment}{symptom\kern0.5em  score\kern0.5em  before\kern0.5em  treatment}\right)\times 100\% $$

#### Part B

##### Primary outcome

The primary outcome of part B is cough symptom score, which will be assessed across baseline, 6 ± 1 days into the intervention, post-intervention (11 ± 1 days) and 2 days post-intervention if necessary. Simplified cough symptom score (SCSS) recommended by Chinese Medical Association [30] is developed based on the Asthma and Cough Symptom Score Estimation Method [31]. It consists of daytime score and nighttime score, ranging from 0 to 3, respectively. The cough symptom score scale is provided in Table 7. SCSS, which is usually used to determine the frequency and diurnal variation of cough, and also to reflect the quality of life, has been verified as reproducible and well-responsive to treatments [32]. Daytime is arbitrarily defined as 8 a.m. to 8 p.m. and nighttime as 8 p.m. to 8 a.m.

**Table 7 Tab7:** Cough symptom score scale

Score	Daytime cough symptom score	Nighttime cough symptom score
0	no cough during the day	no cough during the night
1	occasional cough for short periods	cough for short periods before sleep or occasional cough during the night
2	frequent coughing, which did slightly interfere with usual daytime activities	frequent coughing, which did slightly interfere with sleep
3	distressing coughs, which did seriously interfere with usual daytime activities	distressing coughs preventing any sleep

##### Secondary outcomes

Secondary outcomes of part B include visual analogue scale (VAS) [33], cough recovery rate, time to cough resolution, time to cough relief, TCM curative effect and cough-specific quality of life questionnaire (CQLQ) score (Chinese version). The reliability, validity and responsiveness of the Chinese version of CQLQ had been approved [21]. The production and development of this version were conducted followed the international standard guideline [34] through the comprehensive processes of translation, back-translation, committee review and pre-testing technique use. [name], the author of the original CQLQ, granted the permission to produce the Chinese version [21].

### Safety outcomes

Safety outcomes in this trial include blood routine test, urine routine test, stool routine test, electrocardiogram, liver function test (ALT, AST, STB, ALP, and γ-GT) and renal function test (Bun and Cr). These biological parameters will be monitored both before and after trial intervention. Urine pregnant test (UPT) is supposed to be done before enrolling a female patient of child-bearing age.

### Data management

Completed CRFs will be reviewed by both chief investigators and a qualified research monitor delegated by Beijing Qihuang Medicine Clinical Research Center. CRFs will be delivered for data management. All study data will be entered in computerized database using EpiData 3.1 software by two data mangers independently, and results will be cross checked for accuracy and consistency. Data entered into the database can be accessible only through authorized identification code and password. Moreover, missing data or false data, if there is any, will be detected by designed application program and recorded by data managers, who are qualified to recheck the original CRFs to ensure the correctness, completeness, and consistency of entered data. The database would be locked after data input. Original CRFs will be kept on file in a secure manner at individual participating sites by chief investigators.

### Statistical analysis

Beijing Qihuang Medicine Clinical Research Center is in charge of data statistical analysis. The statistical analysis will be masked. A group of professional statisticians who are independent of all the other process of the study would perform the statistical analysis. Full Analysis Set (FAS) would be applied for all participants who have been randomly allocated and have taken QFGKG or placebo. Non-completers who never use any test drugs will be excluded. Missing values of primary variations will be imputed using the last observation carried forward (LOCF) approach according to intention-to-treat (ITT) principle. Cases in Per Protocol Set (PPS) are those who thoroughly adhere to the protocol without absence of baseline characteristics. Analysis of primary outcome and curative effect will be carried out using FAS approach and PPS approach. Safety Analysis Set (SS) includes all randomized patients who have accomplished at least one study visit. Participating centers are required to sum up participants number in each set and list participants who are removed from PPS. The Chi-square test or Fisher’s exact test will be performed for the categorical variables, and the Student’s t-test will be used for continuous normally distributed variables. For data that is not normally distributed, intra-group or inter-group differences before and after treatment will be analyzed by Wilcoxon rank sum test. The proportion of patients with adverse events in two groups will be compared using the chi-square test or Fisher’s exact test. The statistical significance level is set at *P* < 0.05 and relative risk (RR) with corresponding 95 % confidence interval (CI) to compare dichotomous variables will be calculated. Table 8 shows the method of analysis for specific outcomes.

**Table 8 Tab8:** Outcomes and methods of analysis

Outcome/variable	Hypothesis	Measures	Methods of analysis
Baseline balance test		Quantitative outcomes (age, disease duration, body temperature, heart/respiratory rate, blood pressure)	T-test/Wilcoxon rank sum test
		Qualitative outcomes (gender, marriage, race, previous treatment)	Chi-squared test/Fisher exact test/rank-sum test
Adherence at post-intervention		Percent and cases of adherence in previous 10/14 days < 80 %, > 120 % and 80 %-120 %	Chi-squared test/Fisher exact test
Concomitant treatments		Percent and cases of concomitant treatments	Chi-squared test/Fisher exact test
Intervention duration		Formula: the last day using test drugs-the first day using test drugs + 1	T-test/Wilcoxon rank sum test
Primary			
Time to cough resolution	improvement occurred		Kaplan-Meier method/Log-rank test
Cough symptom score	improvement occurred		T-test/Wilcoxon rank sum test
Secondary			
VAS score	improvement occurred		T-test/Wilcoxon rank sum test
TCM symptom score	improvement occurred		T-test/Wilcoxon rank sum test
TCM curative effect	improvement occurred	Percent and cases of four grades: complete recovery, excellent effect, modest effect and no effect	Cochran-Mantel-Haenszel Chi-squared test
CQLQ score	improvement occurred	Questionnaire	T-test/Wilcoxon rank sum test
Cough disappearance rate	improvement occurred		CMH Chi-squared test
Time to cough relief	improvement occurred		Kaplan-Meier method/Log-rank test

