Patients must provide written informed consent before any study procedures occur. Participants would be excluded if they have any of the following conditions: 1) misdiagnosis; 2) poor drug compliance (taking < 80 % or > 120 % of the required dosage); 3) inability to complete the follow-up; 4) aggravations (such as dyspnea) that happen within 24 h after taking the test drug (on this occasion, patients will be treated with conventional therapies and considered as an invalid case, whose last data would be collected in Full Analysis Set (FAS)); 5) hypersensitivity or other severe adverse reactions; and 6) voluntary withdrawal. The trial will be terminated prior to its planned end date in the context of the following accidents: 1) protocol deviations; 2) inadvisable or flawed protocol; 3) compelling suspension forced by authoritative agencies; and 4) discontinuation decided by the trial sponsor (managerial or financial difficulties).

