### Randomization and blinding

Eligible patients will be randomized in a ratio of 3:1 to QFGKG group or placebo group, with stratification by participating center. A centralized randomization will be employed. The random coding of each center as well as the allocation sequence are generated electronically using SAS 6.12 software. Assignments are concealed in sequentially prepared coded, sealed, opaque envelopes, in which the corresponding intervention group of the randomization list will be found. A professional statistician who is independent of intervention and data collection is appointed to choose appropriate block length to ensure concealment. A group of research assistants who are not involved in recruitment, intervention or assessment of outcomes will prepare the envelopes. Staff responsible for recruitment is not allowed to take part in the group allocation. Only after the former participant is enrolled and his/her baseline testing is completed, the next envelope could be opened by researchers responsible for allocation. Participants will be randomized to the intervention group or the control group in line with numbered envelope under instructions from drug managers at each center. Blind codes along with random seeds and block length will be recorded in duplicate and delivered to Good Clinical Practice (GCP) Centre of West China Hospital and the sponsor for safekeeping. Patients and all engaged personnel including the sponsor remain blind to allocation and intervention throughout the whole process. Placebo will be packaged with imitative similarity in appearance, smell and taste with QFGKG. However, personnel who are designated to prepare drug packaging and labeling will not be blinded. The prepared emergency code-break envelope that contains allocation information, and emergency measures as well as contact details of the responsible department will be distributed to study centers along with drugs. Patients reported side effects will be recorded in the case report forms (CRFs) detailedly by physicians at visit 1 and visit 2. If an unpredictable severe adverse event happens, the chief investigator is qualified to open the emergency envelope and guide physicians to treat the patient according to emergency measures. The patient must be withdrawn and be followed up until he/she recuperates. In this case, the chief investigator should report the case to hospital ethical committee and drug administration agency. The broken code and reasons for unblinding should be recorded on CRF. Meanwhile, severe adverse event report form (SAERF) will also be completed. During the revealing, allocation information must not be disclosed to the patient and any third party.

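### The Safety Analysis Set is defined by completing an undefined study visit instead of by taking study drug, so it does not match the treated population on either reading

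*Protocol article*

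**What the plan says.** The Statistical analysis section gives two membership rules that rest on different criteria. For safety: "Safety Analysis Set (SS) includes all randomized patients who have accomplished at least one study visit". For efficacy: "Full Analysis Set (FAS) would be applied for all participants who have been randomly allocated and have taken QFGKG or placebo". The first depends on attendance, the second on intake. The section also plans a between-group test of the proportion of patients with adverse events, but does not name the set it uses.

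Tables 1 and 2 show Baseline (day 0) in its own column, followed by Visits 1 to 3. Visit 1 is on day 8 ± 1 in part A. In part B it is on day 6 ± 1, and the part B primary outcome text gives the same timing ("6 ± 1 days into the intervention"). Adverse events are ticked at Visits 1 and 2 only, and Randomization and blinding agrees: "Patients reported side effects will be recorded in the case report forms (CRFs) detailedly by physicians at visit 1 and visit 2".

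Study participants lists reasons for removal after enrolment. They include "aggravations (such as dyspnea) that happen within 24 h after taking the test drug", "hypersensitivity or other severe adverse reactions" and voluntary withdrawal. The last data of the 24-hour cases are kept in the Full Analysis Set; the Safety Analysis Set is not mentioned there. For an unpredictable severe adverse event, Randomization and blinding adds: "The patient must be withdrawn and be followed up until he/she recuperates".

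**The concern.** A safety set should contain the people exposed to the product. Here membership depends on reaching a visit, and on the more natural reading the first qualifying visit comes about a week into treatment. Whether a patient gets that far can itself depend on tolerating the drug, which is what the safety comparison is meant to measure. The result can be a patient who counts for efficacy but not for safety.

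Safety is part of the trial objective and is hypothesis 4 at the end of the Background. If early, treatment-ending reactions are more common on QFGKG than on placebo and those patients fall outside the set, the adverse-event comparison moves toward no difference. On the other reading the set gains patients who were never exposed, which lowers the observed rates.

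**Working it through.** There is no figure in the article to reproduce, because the point concerns a definition. The check has two steps: follow each type of patient through the rules, then see how far the comparison could move.

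**Step 1. Membership under each reading of study visit**

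| Patient | Full Analysis Set | Safety set, numbered visits only | Safety set, Baseline counts |
|---|---|---|---|
| Dosed, attends Visit 1 | in | in | in |
| Dosed, reacts, leaves before Visit 1 | in | out | in |
| Randomized, never dosed, no visit after Baseline | out | out | in |

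Neither reading yields exactly the dosed patients. The numbered-visit reading is the more natural one, since the tables and Randomization and blinding both count visits from Visit 1 after a separate Baseline, but the article does not settle it.

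**Step 2. Possible size if the numbered-visit reading applies and the comparison uses this set**

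Inputs from the article: 360 QFGKG and 120 placebo patients (Sample size), pooling two parts of 180 and 60 each (Abstract). Assumed, for scale only: 36 QFGKG and 6 placebo patients with an adverse event, and e QFGKG reactors leaving before Visit 1 with no placebo leavers.

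All dosed patients: 36/360 = 10.0%, 6/120 = 5.0%, relative risk 10.0/5.0 = 2.00.

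Under the visit rule: QFGKG rate = (36 − e)/(360 − e); relative risk = that rate divided by 5.0%.

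| e | QFGKG rate | Relative risk |
|---|---|---|
| 4 | 32/356 = 9.0% | 1.80 |
| 7 | 29/353 = 8.2% | 1.64 |
| 11 | 25/349 = 7.2% | 1.43 |
| 18 | 18/342 = 5.3% | 1.05 |

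The movement in the relative risk depends on unequal early loss. If half the reactors left in both arms, the rates would be 18/342 = 5.3% and 3/117 = 2.6%, with a relative risk of 5.26/2.56 = 2.05. The ratio would hardly change, while the difference in rates would shrink from 5.0 to 2.7 percentage points.

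**Step 3. If Baseline counts**

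With u never-dosed patients in the QFGKG arm the rate becomes 36/(360 + u), which is below 10.0% for any u above zero. If the never-dosed share is the same in both arms, both rates fall by the same factor and the ratio is unchanged. The article gives no basis for a value of u.

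**The case against.** The strongest reply is that little need be lost. Baseline is an attended appointment with consent, laboratory tests, ECG, randomization and dispensing, and it stands under the same time-point heading as Visits 1 to 3. If it counts, early reactors stay in. That stands as a reason not to assert the numbered-visit reading as fact. It does not rescue the rule, because never-dosed patients then enter.

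A reader might infer that the most severe early reactions vanish from the trial. The documents do not support that. Under Randomization and blinding, an unpredictable severe event leads to a case report form entry if the code is broken, a severe adverse event form, notification of the ethics committee and the drug agency, and follow-up to recovery. Interventions also has centres record dropouts with reasons and side effects during treatment, so recording is not confined to Visits 1 and 2. What may be lost is the patient's place in the comparison.

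A reader might also infer that the removals in Study participants all happen before Visit 1. Only the aggravation item has an early time limit. Hypersensitivity, severe reactions and voluntary withdrawal carry no timing, and a patient removed for one of them after Visit 1 is in the safety set on any reading.

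Finally, the adverse-event test names no analysis set. That it uses the Safety Analysis Set is a reasonable inference, since the set has no other evident purpose, but it is not stated.

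**Conclusion.** The definition is wrong as written: it is not tied to exposure, its key term is undefined, and both available readings give a population other than the treated one. This is a rule the article states, so it cannot be put down to detail left for an analysis plan.

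The consequence is conditional. Bias toward no difference requires that study visit means the numbered visits, that the adverse-event comparison uses this set, and that more reactors leave before Visit 1 on QFGKG than on placebo in proportion to their number. The article gives no adverse-event rate and no early-withdrawal rate, so the size is unknown. The range of 1.80 to 1.05 against a true 2.00 rests on assumed counts with no placebo leavers. Its lower end, where the QFGKG rate falls from 10.0% to 5.3%, is an extreme case and should not be read as an estimate.

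**What to change.** Replace the definition with: all randomized patients who took at least one dose of QFGKG or placebo, regardless of visits completed. State that the adverse-event comparison uses this set. Count every adverse event recorded from first dose, including those recorded at withdrawal or between visits.

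The cost is a few sentences in the protocol or analysis plan. No added patients or assessments are needed, because intake, dropouts with reasons and side effects during treatment are already to be recorded. The change should be made before database lock and unblinding. The article reports 318 of the planned 480 patients included, with recruitment still in progress.

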**Methods/Design:**

This is a multicenter, phase III, randomized, double-blind, parallel-group, placebo-controlled clinical trial, comprising two simultaneously conducted study parts, part A and part B, intending to investigate two primary outcomes, *i.e.* time to cough resolution and cough symptom score, respectively. A total of 480 patients, aged 18 to 65 years, who complain of an ongoing persistent cough that has been lasting ≥3 weeks, will be recruited from six participating sites and then randomized to receive QFGKG 12.0 g twice daily or placebo 12.0 g twice daily. Each part will enroll 240 patients, with 180 patients being allocated to the QFGKG group and 60 to the placebo group.

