## Background

Cough is the most common symptom presenting to primary healthcare services. Postinfectious cough (PIC) is considered as one of the top causes of subacute cough, which occurs in 11 to 25 % of patients with upper respiratory tract infection (URTI) [1, 2]. It involves a persistent cough lasting ≥3 weeks or even months [3] (but normally < 8 weeks) secondary to the acute symptoms of a common cold or upper respiratory tract infection (URTI) [4, 5]. Although PIC is always self-limited and is not associated with severe debilitation or mortality, persistent cough may impair the quality of daily life [4]. Therefore, many patients with PIC are frequently impelled to seek medical help [6].

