## Methods/Design

### Study designs

This trial is designed as a randomized, double-blind, placebo-controlled, parallel, phase III, superiority trial, with allocations stratified by participating centers and randomization performed as block at a ratio of 3:1, adhering to the recommendation of “CONSORT statement” [23] and “SPIRIT statement” [24]. As to the allocation ratio, generally speaking, for a superiority trial using placebo as a control intervention, 3:1 is recommended by Provisions for Drug Registration (http://www.sda.gov.cn/ypzcgl/ml.htm), taking into full consideration of statistical significance, ethical requirement and risk-cost relationship. This trial consists of two simultaneously conducted study parts (part A and part B), currently involving six participating centers across China: West China Hospital of Sichuan University, Tangdu hospital of The Fourth Military Medical University, Affiliated Hospital of Jiangxi University of TCM, the Second Affiliated Hospital of Tianjin University of TCM, Affiliated Hospital of Inner Mongolia Medical University, and the First Affiliated Hospital of Henan University of TCM. These centers were defined primarily geographically. In each participating center, a chief investigator will be appointed to be responsible for the whole clinical process (subject recruitment, intervention, follow-up, and data collection), adhering to the study protocol. All personnel involved in this trial will be trained prior to trial initiation. Training program is about study protocol and relevant skills, especially the skill of TCM syndrome differentiation. Staff placement and individual responsibility will also be elaborated in the training session. Besides, investigator’s brochure developed by the sponsor to facilitate the smooth running of the trial will also be provided. This protocol is designed largely depending on the results of previous phase II trial. Both study parts have been registered with Chinese Clinical Trial Registry (http://www.chictr.org). This protocol has two amendments. The schematic diagram and flow chart of study process are shown in Tables 1, 2 and Fig. 1.

**Table 1 Tab1:** Schematic diagram of part A

Phase	Supervision period			
Time-point	Baseline	Visit 1	Visit 2	Visit 3
Day	0	8 ± 1	15 ± 2	Follow-up
Basic history collection	×			
Informed consent	×			
Demographics	×			
Enrollment based on the inclusion/exclusion criteria	×			
Coexisting diseases or symptoms	×			
Concomitant treatments		×	×	

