
### Sample size

The latest edition of Provisions for Drug Registration issued by CFDA recommends a minimum number of 300 for subjects enrolled in the trial group in a phase III clinical trial. Sample size calculation of this trial results in 24 patients in total for part A (18 in the QFGKG group and 6 in the placebo group) and 56 patients in total for part B (42 in the QFGKG group and 14 in the placebo group), respectively. Obviously, the calculated patient number in the QFGKG group is much smaller than the recommended one. Given the above, we set the sample size according to the Provisions for Drug Registration. 480 patients in total would be included, with 360 being assigned to the QFGKG group and 120 being assigned to the placebo group, considering a maximal dropout rate of 20 %. Calculation assumed an 80 % power for a two-sided log-rank test at a 5 % significance level.

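### Where the t-test branch compares arms of 180 and 60, the protocol names Student's equal-variance form; the unequal-variance form is safer and costs almost nothing (minor)

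*Protocol article*

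**What the plan says.** The Statistical analysis section chooses the test for a continuous outcome by its distribution. The normal branch reads "Student’s t-test will be used for continuous normally distributed variables". The other branch reads "For data that is not normally distributed, intra-group or inter-group differences before and after treatment will be analyzed by Wilcoxon rank sum test". Table 8 repeats the pair as "T-test/Wilcoxon rank sum test" for part B's primary cough symptom score and for the VAS, TCM symptom and CQLQ scores. It does not say which variance form the t-test takes.

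The Study designs section has "randomization performed as block at a ratio of 3:1", and the abstract gives the arms of each part "with 180 patients being allocated to the QFGKG group and 60 to the placebo group". The only interval that the section plans is for binary outcomes: "relative risk (RR) with corresponding 95 % confidence interval (CI) to compare dichotomous variables will be calculated". The article gives no SD for either arm and mentions neither a check of equal variances nor an unequal-variance test.

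**The concern.** Student's t-test estimates one common variance. With equal arms it does little harm if that assumption fails. With three times as many patients on QFGKG it matters. About three quarters of the pooled variance comes from the QFGKG arm, while the sampling error of the difference depends mainly on the 60 placebo patients. If placebo scores are the more spread out, the pooled standard error is too small. If QFGKG scores are, it is too large.

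Unequal spread is plausible here. Part B's score is a whole-number total from 0 to 6, entry needs at least 4, and the Background says that "PIC is always self-limited". A drug that brings more patients to 0 could compress the QFGKG distribution against the floor. A normality check does not guard against this, because it looks at shape and not at whether the arms share a variance. At stake is the accuracy of the standard errors and P values from the t-test branch, and of any interval for a mean difference reported from it.

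**Working it through.** **No figure in the plan to reproduce.** The plan states no SD. The calculated size for part B, 56 patients (42 + 14), comes with no mean difference or SD. The only basis named is "Calculation assumed an 80 % power for a two-sided log-rank test at a 5 % significance level", which does not describe a comparison of mean scores. If a two-means formula is assumed, 14 controls at 3:1 imply a standardised difference of √[(1.960 + 0.842)² × (4/3) / 14] ≈ 0.86. That says nothing about the ratio of the two SDs, so the ratio has to be assumed.

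**Inputs.** Arm sizes are 180 and 60 (abstract). The QFGKG SD is set to 1 and the placebo SD to k, with k assumed between 0.67 and 1.5.

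**Formulas.**
- Pooled variance: s² = (179 × 1 + 59 × k²) / 238
- Pooled SE: √[s² × (1/180 + 1/60)]
- True SE: √(1/180 + k²/60)
- Approximate coverage of a nominal 95% interval: 2Φ(1.970 × pooled SE / true SE) − 1, where 1.970 is the t critical value on 238 degrees of freedom

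**Worked case, k = 1.5.** s² = (179 + 59 × 2.25) / 238 = 1.310. The pooled SE is √(1.310 × 0.02222) = 0.1706. The true SE is √(0.00556 + 0.03750) = 0.2075. The quotient is 0.82, and coverage is 2Φ(1.620) − 1 ≈ 89.5%.

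| Placebo:QFGKG SD ratio (assumed) | Pooled SE | True SE | Pooled / true | Coverage |
|---|---|---|---|---|
| 0.67 | 0.1385 | 0.1142 | 1.21 | 98.3% |
| 0.80 | 0.1423 | 0.1274 | 1.12 | 97.2% |
| 1.00 | 0.1491 | 0.1491 | 1.00 | 95.1% |
| 1.25 | 0.1591 | 0.1778 | 0.90 | 92.2% |
| 1.50 | 0.1706 | 0.2075 | 0.82 | 89.5% |

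(The 95.1% at equal SDs shows the small error of the approximation.)

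**Is the allocation the cause?** At 120 and 120 the quotient is 1.00 for every k. At 144 and 48 (both arms reduced by 20%) it is the same as at 180 and 60 to two decimals. The bias therefore follows the 3:1 ratio and hardly depends on total size. For the same reason, the per-centre numbers under Study participants (60 and 80 at six centres, so 360 and 480, against 240 per part elsewhere) do not affect it.

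**Does the unequal-variance form cure it?** In 100,000 simulated trials per setting with normal data, its two-sided error stayed between 4.9% and 5.1% for SD ratios from 0.5 to 2. In 8,000 simulated trials with a 0 to 6 integer score, equal means and SDs of 1.0 (QFGKG) and 1.5 (placebo), it rejected in 5.2%, against 10.7% for the pooled test.

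**Cost at equal SDs.** Welch degrees of freedom are (1/180 + 1/60)² / [(1/180)²/179 + (1/60)²/59] ≈ 101. The critical value is then 1.984 instead of 1.970, a factor of 1.007.

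**The case against.** The case on the other side is substantial, and most of it stands.

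- **The t-test is only one branch.** A reader might infer that the plan fixes the pooled test as part B's primary analysis. It does not. A score with seven possible values may well be judged non-normal and go to the rank test, so the bias may never reach the primary result.
- **Equal variance is not written out.** It is read from the name Student's, and Table 8 says only t-test. The variance form is often left to the analysis plan. This narrows the point but does not remove it, because the article does name a test whose ordinary meaning is the pooled form.
- **Confidence intervals.** A reader might conclude that the planned intervals are wrong. None is planned for a mean difference, so the coverage figures describe only intervals that might be reported later.
- **False positives.** A reader might conclude that the trial's error rate rises to about 10.5% (1 − 0.895 at a ratio of 1.5). That needs equal means with unequal spread. The mechanism suggested for unequal spread also moves the mean. If QFGKG has no effect at all, the two distributions are the same and the pooled test keeps 5%.
- **Bias in favour of QFGKG.** The direction is not established. In an assumed beta-binomial model of a 0 to 6 score, means of 0.6 and 1.5 give an SD ratio of 1.44, but means of 2 and 3 give only 1.06, and 2.5 and 3.5 give 1.00. The plan also carries the last observation forward for missing primary values, so treated dropouts stay in the full analysis set, possibly with earlier and higher scores. If 20% of each arm carried scores of 3 to 5 (assumed), the ratio of 1.44 would fall to between 0.94 and 1.14.

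What survives is narrow. Where a t-test compares arms of 180 and 60, the named form depends on an equal-variance assumption that the article gives no grounds for.

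**Conclusion.** The point holds in limited form and is minor. Within the t-test branch, the pooled standard error would be about 1.21 to 0.82 times the true one for assumed placebo:QFGKG SD ratios of 0.67 to 1.5, with coverage of about 98% to 89.5%. This rests on two things: reading Student's in its usual sense, and treatment altering spread as well as mean. The article gives no SDs, so neither the size nor the direction can be settled from it. It does not support saying that part B's primary analysis is invalid, that its type I error is inflated under no effect, or that the result will favour QFGKG.

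**What to change.** In the Statistical analysis section and in Table 8, state that wherever a t-test compares the two arms it is the unequual-variance (Welch/Satterthwaite) form, and that any interval for a mean difference is built the same way. The choice between t-test and rank test can stay as it is, since this point gives no reason to change it. The cost is one wording change and one software option, with no new data. If the SDs turn out equal, the critical value is about 0.7% larger (1.984 against 1.970).
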